#### Sensory discomfort evaluation.

Sensory discomfort will be assessed using a horizontal numeric discomfort rating scale. The scale will be presented in printed form on standard 10.0 cm paper, where “0” indicates no discomfort and “10” represents the worst imaginable discomfort. Participants will be asked to rate their perceived sensory discomfort for both interventions (i.e., TEPNS and TDES) at three time points: (i) Baseline – before the start of the intervention; (ii) Measure 5 – the first re-evaluation, conducted between the 4th and 5th minute of the intervention; and (iii) Measure 10 – the final re-evaluation, conducted during the last minute of the intervention [27].

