### Intervention

The intervention will be conducted in two different times, depending on the randomization sequence, and may begin with either TEPNS or TDES. A 1-hour washout period will be conducted between the two interventions. During interventions, participants will be instructed to breathe normally at tidal volume, using the perception of the electrical current as a cue for the onset of inspiration. This ensures synchrony with the stimulation cycle (“on” and “off” times), without altering the participant’s natural respiratory rhythm or pattern. For both the TEPNS and TDES, electrical stimulation will be applied continuously for 10 minutes in a single session.

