### Outcome measures

#### Diaphragmatic ultrasonography.

Diaphragmatic assessments will be performed using a LOGIQ E^®^ (R7) ultrasound system equipped with linear (GE12L-RS, 13 MHz) or a convex transducer (C1-5-D), in conjunction with water-based gel. Participants will be evaluated in supine position with a 30 degrees trunk inclination. Diaphragmatic mobility, thickness, and thickening fraction will be assessed. To measure tidal volume during the intervention, a facial mask will be connected to a ventilometer and a HEPA-filtered. The facial mask will be placed by the evaluator one minute before the assessment, and during two specific intervals: between the 4th and 5th and between the 9th and 10th minute of the intervention. Ultrasound evaluations will be conducted during spontaneous ventilation at tidal volume during both intervals, according to the randomization protocol.

Measurements of diaphragm mobility, thickness, and thickening fraction will be averaged from multiple respiratory cycles within the following three time points: (i) baseline (pre-intervention), (ii) 4–5 minutes into the intervention, and (iii) 9–10 minutes post-intervention. All ultrasound images will be exported to a secure storage device designated for research purposes only, with access restricted to authorized study personnel and researchers. While blinding is not feasible during image acquisition, a blind evaluator–who is not involved in the intervention or image collection–will perform the image analysis.

Diaphragmatic mobility will be assessed using a convex transducer (2–6 MHz) positioned in the right subcostal region along the mid-clavicular line, angled cephalically (**Fig 4A****-****4C**). Initially, B-mode ultrasound will be used to locate the diaphragmatic hemi-cupola. Once identified, M-mode will be employed to measure respiratory excursions, using the inferior vena cava and gallbladder anatomical landmarks. Mobility will be quantified as the vertical distance between the baseline position during expiration and the point of maximal diaphragmatic displacement during inspiration [22,23].

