### Safety assessment

Safety criteria will be evaluated by monitoring for adverse events during the intervention period. Criteria for adverse events include: mean arterial pressure < 65 mmHg, heart rate > 140 bpm or < 50 bpm, occurrence of arrhythmias, oxygen saturation < 92%, elevated body temperature (> 37.7°C), reported discomfort > 7 on the visual analog discomfort scale, and burns or skin injury at the electrode application site. Participants’ vital signs will be continuously monitored throughout the intervention and recorded at 2-minute intervals using a multiparameter monitor (General Electric CARESCAPE Monitor B650).

All adverse events will be recorded and classified according to the World Health Organization’s patient safety guidelines [28], which ranges from “No harm” (no symptoms detected or observed, no treatment required) to “Death” (event caused or significantly contributed to short-term mortality). Adverse events will be monitored only during the intervention, as no long-term side effects related to transcutaneous electrical stimulation have been reported in the literature. Any adverse events will be documented, classified, and reported to the institutional authorities responsible for ethical oversight and study approval.

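### No discomfort rating is scheduled when the current is set or in the first 4 minutes, so early discomfort above 7 can be missed; the threshold also sits on two differently named scales

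*Protocol article*

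**What the plan says.** All references are to the Methods of the protocol article unless noted.

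- **Rating times (Sensory discomfort evaluation).** There are three: "Baseline – before the start of the intervention"; "the first re-evaluation, conducted between the 4th and 5th minute of the intervention"; and "the final re-evaluation, conducted during the last minute of the intervention".
- **Session length (Intervention).** For each technique, "electrical stimulation will be applied continuously for 10 minutes in a single session".
- **Intensity (the TEPNS and TDES sections).** Both raise the current to the most the participant will tolerate, subject to conditions on which muscles contract. Neither says when this happens relative to minute 0, or whether the level is adjusted later.
- **Event definition (Safety assessment).** The criteria include "reported discomfort > 7 on the visual analog discomfort scale". Adverse events are monitored over the intervention period. Vital signs are watched continuously and "recorded at 2-minute intervals using a multiparameter monitor". Discomfort is not named in that 2-minute schedule.
- **Scale (Sensory discomfort evaluation).** "Sensory discomfort will be assessed using a horizontal numeric discomfort rating scale", running from 0 to 10. Safety assessment calls it a visual analog scale.
- **What else happens at the rating times (Diaphragmatic ultrasonography).** "The facial mask will be placed by the evaluator one minute before the assessment, and during two specific intervals", namely minutes 4–5 and 9–10, when ultrasound is also acquired.

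**The concern.** Perceived discomfort is a secondary objective in the Abstract, an adverse-event criterion, and one of the variables to be correlated with stimulation intensity. The Discussion says that the safety data will inform later studies in patients. Yet no score is scheduled at the point where the current is taken to the tolerance limit, and none follows until minute 4.

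The criterion needs a number on a scale. An unprompted complaint in the first minutes has no number unless someone asks for one, and the article does not say that anyone will. The Statistical analysis section promises systematic recording of adverse events, which volunteered reports alone do not provide.

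The error can run only one way. The highest of two ratings cannot exceed the highest of those two plus a third, so a further rating can only keep or raise the number of participants with an event. If early discomfort is missed, both techniques look better tolerated than they are.

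**Working it through.** The protocol states no discomfort rate or adverse-event rate, so there is no figure to reproduce. The check has three parts.

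**1. Coverage of the session (figures from the protocol)**

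- Cycle length: 1 + 1 + 1 + 2 = 5 s, so 60 / 5 = 12 stimuli per minute, as the protocol states.
- Stimuli before minute 4: 4 × 12 = 48 of 10 × 12 = 120, or 40%.
- The two rating windows during stimulation cover 2 of 10 minutes, or 20%.

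**2. Sensitivity of the event count to the time course (all score inputs assumed)**

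For each simulated participant, the rating at time *t* is *m* + *d*(t) + *u* + *e*(t), rounded to a whole number and limited to 0–10. Here *m* is the mean when intensity is set, *d* is the later change (0 at setting), *u* is the participant effect and *e* is independent error. The total SD is 2 and the within-person correlation is 0.8, so Var(*u*) = 0.8 × 4 = 3.2 and Var(*e*) = 0.2 × 4 = 0.8. An event is any rating above 7. Each scenario used 400,000 simulated participants. Volunteered reports are not modelled.

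| Change at minute 4–5, then last minute | Planned two ratings, *m* = 6 | With a third at intensity setting, *m* = 6 | Share captured, *m* = 5 to 7 |
|---|---|---|---|
| −1, −2 | 11.6% | 24.8% | 37–57% |
| −0.5, −1 | 19.0% | 27.9% | 61–75% |
| 0, 0 | 30.4% | 34.8% | 84–90% |
| +0.5, +1 | 45.7% | 47.2% | 96–98% |
| +1, +2 | 63.0% | 63.3% | 99–100% |

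In the flat row nothing peaks early. The gain there comes only from having a third look at a variable score.

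**3. What the threshold means on each scale (same assumed mean 6, SD 2, single rating)**

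- On a continuous line, above 7: (7 − 6) / 2 = 0.5, upper tail 0.309.
- On whole numbers, above 7 means 8 or more, which after rounding is 7.5 or more: (7.5 − 6) / 2 = 0.75, upper tail 0.227.

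Under these assumptions the same underlying discomfort gives an event in 31% or 23% of ratings, depending on which name is taken literally. The protocol does not say whether whole numbers are required.

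**The case against.** The strongest reply is that the protocol does not say when discomfort peaks, and that rating times are a matter of preference.

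- **Peak.** A reader might infer that peak discomfort is never rated. The document does not support that: a peak at minute 4–5 or in the last minute would be rated. The Discussion points both ways. It justifies a short session as preventing discomfort, which suggests build-up, and as limiting adaptation, which suggests decline. It is also not stated that intensity is set at minute 0, so the gap between setting and first rating is unknown.
- **Undercount.** A reader might infer that the event is necessarily undercounted. Safety assessment does not limit the criterion to scheduled ratings, so a score volunteered at another time could count. How such reports are sought may be left to the full protocol, which is not shown.
- **Singled-out criterion.** Discomfort is not the only criterion outside the 2-minute schedule. That schedule covers vital signs, and burns and skin injury have none either.
- **Comparison.** Both techniques share the same rating times, mask and ultrasound in the same participant. A biased comparison would need different time courses, for which the document gives no evidence. That mask or probe discomfort enters the score is likewise an inference.
- **Burden.** Extra ratings interrupt participants who are using the current as their cue to inhale.

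All of this limits the claim, but the gap remains. The article states the rating schedule outright, so it is not a detail left out, and that schedule contains no score at intensity setting or before minute 4.

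**Conclusion.** The point holds as a gap in ascertainment. The planned schedule can miss discomfort above 7 arising when the current is set or in the first 4 of 10 minutes, unless the participant reports it unprompted and it is scored. On the assumed scores the loss is large if discomfort falls from onset, modest if it is flat and close to none if it rises. The direction is certain, because added ratings cannot lower the count. The size is not, because the mean, SD, correlation and time course are all assumptions. A single figure for the share of events missed would follow from the assumed direction of change and should not be quoted as a finding. Bias between TEPNS and TDES is a possibility only.

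The mismatch in scale names is a plain inconsistency between two sections, and it bears directly on the event definition.

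**What to change.** 1. Add one discomfort rating for each technique once intensity has been set, at the start of the 10 minutes.
2. Where feasible, add one at an existing 2-minute vital-sign recording outside the mask and ultrasound windows. If recordings run from the start of stimulation, minute 2 falls inside the present gap.
3. Keep the minute 4–5 and last-minute ratings while stimulation is on. Moving the final one to after image acquisition would put it at or past the end of stimulation.
4. Count the discomfort event on the highest rating during stimulation, including any volunteered report scored on the scale, and say how such reports are scored. Also report the intensity-setting rating separately, since it comes from a procedure that seeks the tolerance limit.
5. Use one scale name in Sensory discomfort evaluation and Safety assessment, and state what above 7 means on it.

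The cost is a few seconds per added rating, brief extra interruptions, a small form change and probably a higher reported discomfort event rate. The change concerns measurement only and leaves the stimulation procedure as it is.

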### Safety assessment

Safety criteria will be evaluated by monitoring for adverse events during the intervention period. Criteria for adverse events include: mean arterial pressure < 65 mmHg, heart rate > 140 bpm or < 50 bpm, occurrence of arrhythmias, oxygen saturation < 92%, elevated body temperature (> 37.7°C), reported discomfort > 7 on the visual analog discomfort scale, and burns or skin injury at the electrode application site. Participants’ vital signs will be continuously monitored throughout the intervention and recorded at 2-minute intervals using a multiparameter monitor (General Electric CARESCAPE Monitor B650).

All adverse events will be recorded and classified according to the World Health Organization’s patient safety guidelines [28], which ranges from “No harm” (no symptoms detected or observed, no treatment required) to “Death” (event caused or significantly contributed to short-term mortality). Adverse events will be monitored only during the intervention, as no long-term side effects related to transcutaneous electrical stimulation have been reported in the literature. Any adverse events will be documented, classified, and reported to the institutional authorities responsible for ethical oversight and study approval.

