### Transcutaneous diaphragmatic electrical stimulation (TDES)

The electrical parameters for TDES consist of biphasic waveform with a stimulation frequency of 30 Hz, a pulse width of 400 μs, a rise time of 1.0 second, an “on” time of 1.0 second, a fall time of 1.0 second, and an “off” time of 2 seconds, resulting in 12 stimuli per minute [19]. For TDES application, two self-adhesive electrodes (5.0 x 5.0 cm) will be placed bilaterally in the parasternal region, positioned inferior and lateral to the xiphoid process. An additional pair of electrodes will be placed bilaterally in the intercostal space between the 6th and 7th ribs, along the midaxillary line (**Fig 3D**). Electrode positioning will be guided by an initial ultrasound evaluation to identify the region of greatest visible diaphragmatic apposition. The stimulation intensity, measured in milliamperes (mA), will be gradually increased to the maximum level tolerated by the participant, until visible diaphragmatic contraction is achieved without concomitant contraction of abdominal muscles.

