Despite the strengths, some limitations should be acknowledged. The study will be conducted with a sample of health volunteers, which may limit the generalizability of the findings to critically ill patients. Healthy volunteers were defined as the initial study population to allow a controlled evaluation of feasibility, safety, and discomfort, prior to assessing the outcome of the intervention in critically ill patients. However, this approach may limit the external validity and generalizability of the findings. The nature and characteristics of the intervention was not designed to evaluate long term clinical outcomes. The findings of this study should be interpreted within the context of the specific sample, as they are limited to participants recruited from two hospitals in São Paulo, Brazil. Therefore, further studies with larger sample sizes and conducted across different geographic settings are warranted to confirm and expand upon these results, as well as to better evaluate potential differences between TEPNS and TDES. In addition, this study includes only adults (aged <60 years), which may limit the generalizability of the findings to older populations.

Furthermore, our study did not include a sham stimulation condition, as the primary objective was to compare the efficacy of two techniques already used in clinical practice for non-invasive diaphragmatic stimulation. Additionally, participant blinding was not feasible, since the stimulation methods (TEPNS and TDES) are applied to different anatomical locations, making it possible for participants to distinguish between the interventions.

Despite its limitations, this trial is expected to generate clinically relevant data, particularly regarding the safety of the interventions, which will be important to inform future studies in patient populations. The evidence generated by this trial will be especially important for advancing strategies aimed at mitigating respiratory muscle weakness.

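### Adverse events are monitored only during each intervention, so skin injury found at electrode removal and short-term reactions in the washout or after the second session may go unrecorded

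*Protocol article*

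**What the plan says.** The Safety assessment section of the protocol article sets the window twice: "Safety criteria will be evaluated by monitoring for adverse events during the intervention period", and later "Adverse events will be monitored only during the intervention". The restriction is justified in one clause: "as no long-term side effects related to transcutaneous electrical stimulation have been reported in the literature". The listed adverse events are mostly vital-sign limits (blood pressure, heart rate and rhythm, saturation, temperature). A discomfort score above 7 and "burns or skin injury at the electrode application site" are also listed.

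On timing, the Intervention section says that "electrical stimulation will be applied continuously for 10 minutes in a single session" for each technique, and that "A 1-hour washout period will be conducted between the two interventions".

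On electrodes, the TDES section says that "two self-adhesive electrodes (5.0 x 5.0 cm) will be placed bilaterally" near the xiphoid process, and adds a second bilateral pair on the midaxillary line. The TEPNS section describes a 2 mm spherical active electrode at the neck and a passive electrode at the acromion, whose type and size are not given.

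Safety is named as a secondary objective in the Abstract. The Discussion says that "this trial is expected to generate clinically relevant data, particularly regarding the safety of the interventions", and that these data will be important for later studies in patients.

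**The concern.** The reason given does not match the restriction. That no long-term effects have been reported may justify not following participants for days or weeks. It says nothing about the minutes after the electrodes come off, the washout hour, or the time before the participant leaves.

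The window also sits badly with the protocol's own list of events. Skin under an adhesive pad cannot be seen while the pad is in place, so an injury there is normally found at removal. The article describes no inspection at that moment and does not say whether removal belongs to the intervention. Both techniques are run at the highest intensity the participant tolerates, so local skin effects are a realistic thing to look for.

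What is at stake is how a low event count can be read. If few events are reported, a reader planning a study in patients cannot tell whether few occurred or whether nobody was asked to look when they would have appeared. A delayed reaction to the second technique has no later observation point at all. One to the first technique might surface during the second, and the article gives no rule for which technique it counts against.

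**Working it through.** The protocol gives no expected event rate or safety sample size, so there is no figure of its own to reproduce. The check compares sections and adds one piece of clock arithmetic.

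**Inputs**
- Stimulation per technique: 10 minutes (Intervention)
- Washout between techniques: 60 minutes (Intervention)
- Adverse event window: the intervention only (Safety assessment, stated twice)

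**Clock time covered**, taking the intervention to mean the 10 minutes of stimulation:
- Monitored: 10 + 10 = 20 minutes
- Shortest span from start of first stimulation to end of second: 10 + 60 + 10 = 80 minutes
- Covered: 20 / 80 = 25%. Not covered: 60 / 80 = 75%, plus all time after the second session
- With the washout included: 80 / 80 = 100% of that span

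**Sections side by side**

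| Period | Observation described in the article |
|---|---|
| During stimulation | Vital signs monitored continuously and recorded every 2 minutes; discomfort rated at minutes 4 to 5 and in the last minute |
| Electrode removal | None described; not stated whether it is part of the intervention |
| Washout hour | None described, apart from a baseline discomfort rating before the second technique, which is not designated an adverse event check |
| After the second session | None described |

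The vital-sign and discomfort criteria fit the window well, because they are measured while stimulation runs. The skin criterion does not fit it for TDES, where pads cover four sites until removal. It may not fit for TEPNS either, since the passive electrode is undescribed and the active tip also rests on the skin.

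**Effect on the reported frequency.** If a proportion p of events arises or becomes visible only outside the window and is therefore not recorded, the recorded frequency is (1 − p) times the true one. The document gives nothing from which to estimate p; it could lie anywhere from 0 to 1 and may differ by event type. Its value for each technique is also unknown, so a difference in detection cannot be given a direction or a size.

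**The case against.** The strongest reply has four parts.

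1. The article says during the intervention, not while current flows, and does not say that the intervention ends before the pads are removed. Listing skin injury as a criterion presupposes that someone looks at the site, and the same section promises that any adverse event will be documented. The schedule figure is not available, and a skin-check step is the kind of detail a full protocol may hold. This stands as far as it goes: injuries *may* be missed, and it is not shown that they will be. It does not rescue the window itself, which is an explicit rule with a stated reason and not a detail lost in condensing.

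2. A reader might infer that the comparison of techniques is biased against detecting harm from TDES, because its pads cover more skin than a 2 mm tip. The document does not support that. The passive TEPNS electrode could also be a covering pad, and adverse events are to be analysed descriptively, with exploratory correlations and no formal safety comparison.

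3. A reader might take the 25% to mean that three quarters of events are lost. It does not mean that. Most criteria belong to the stimulation period, and the Discussion argues that effects on muscle activation, ventilation and hemodynamics are mainly acute and fade shortly after stimulation stops. That argument is fair for those effects, but it does not address skin.

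4. Extending full vital-sign monitoring through the washout would add about 60 minutes of monitoring per participant. It could also credit ordinary resting values, such as a heart rate below 50, to the preceding stimulation. This is right, and the change proposed here does not ask for it.

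**Conclusion.** The point holds as a fault in a stated design choice. The adverse event window excludes the washout and all time after the second session. It makes no provision for inspecting skin after electrode removal, and the reason offered covers only long-term effects. Short-term skin injury and delayed reactions may therefore be missed and the event frequency understated, although safety is a secondary objective and is offered as evidence for patient studies.

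The size is known only in clock time: 20 of at least 80 minutes, with nothing after the second session. This rests on reading the intervention as the 10-minute stimulation, which is the natural reading but is not defined. If removal is meant to be included, the skin part of the concern shrinks to a clarification, while the washout and post-session gaps remain. The number of events missed cannot be estimated from the document. The efficacy outcomes and their analysis are not touched. The change should be made but does not threaten the trial.

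**What to change.** Amend the Safety assessment section in three respects.

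- **Skin check.** Inspect and record the skin under every electrode (TEPNS active and passive, all TDES pads) when it is removed, in the same way for both techniques.
- **Recording window.** Record adverse events that staff observe or the participant reports from the start of each stimulation through the washout, with a brief check before the second intervention, and after the second intervention until the participant leaves. Continuous vital-sign monitoring can stay limited to stimulation.
- **Attribution.** Report each event under the stimulation it follows.

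The cost is a few minutes of existing staff time. The drawback is that an event late in the washout, or one first noticed during the second intervention, may be hard to attribute; recording its time of onset would let readers judge. No stimulation procedure or efficacy outcome changes. Recruitment is expected to run to July 2027, so an amendment would still apply to participants yet to be enrolled.
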